### Recruitment {15}

The trial plans to recruit from 12 to 14 sites over 36 months. The sample size of 565 requires that each site will recruit an average of 41 participants. Assuming the majority of sites recruit for a 24-month period due to staggered set-up, sites will recruit on average 2 participants per month.

An internal pilot will assess progression criteria on recruitment rates at nine months from the start of recruitment. Rates will be calculated from recruitment in each of the six sites in months 4 to 9 to allow time for recruitment to stabilise. The average number of participants recruited per month will be assessed as: red if < 12, amber if 12–19 and green if ≥ 20. Assuming six sites are open to recruitment, the criteria would be approximately equivalent to assessing monthly recruitment per site as: red if < 2, amber if 2–3.2, green if ≥ 3.3 participants per site per month. The internal pilot will inform a decision on continuation or modification of the trial, with an additional 9 months of recruitment anticipated thereafter. If the recruitment criterion is amber, we will review trial processes comprehensively, with the TSC and the funder, to see if modifications could be made to improve recruitment rates. If the recruitment criterion is red, the TSC and the funder will consider not continuing the trial.

## Assignment of interventions: allocation

### Sequence generation {16a}

Participants will be randomised to standard care plus intervention or standard care alone on a 1:1 basis. Randomisation will use minimisation with a random element, balanced on stratification factors of site, gender and baseline CORE-OM score (< 25 or ≥ 25, using derived score with a range of − 0 to 40).

### Concealment mechanism {16b}

The Clinical Trials Research Unit’s (CTRU) online 24-h computer-generated randomisation system will be used to generate the treatment allocation and ensure allocation concealment. Allocation information will only be released after the patient has been consented and recruited into the trial, and after all baseline measurements have been completed.

### Implementation {16c}

Randomisation will be requested by the study researcher at site using the CTRUs online randomisation system. An automated email will be sent from the randomisation service to the researcher responsible for recruitment and the site PI confirming randomisation and the participant’s allocation. Following randomisation, the researcher will contact participants and therapists to inform them of their allocation. A letter will also be sent to the participant’s GP informing them of their participation in the trial.

Participants allocated to standard care plus intervention will be further randomised to a trained therapist to receive one of the possible psychological therapies available for delivery within the site: CBT, PIT or ACT. Randomisation to therapist will be via simple randomisation stratified by site and will be performed concurrently within the CTRU online randomisation system. To allow for cases where the randomised therapist cannot deliver the intervention (e.g. due to participant preference on therapist gender, or therapist capacity), a backup randomised ordered list of all remaining therapists at site will also be generated and the researcher will liaise with the service lead and therapists in order until an allocated therapist is confirmed.

## Assignment of interventions: blinding

### Who will be blinded {17a} and procedure for unblinding {17b}

Due to the nature of the intervention, blinding of therapists and participants will not be possible therefore there is no requirement for emergency unblinding procedures in this study. Principal investigators and supervisors at sites will not be blinded since they may advise on risk incidents during therapy. Researchers involved in the organisation of therapy sessions will not be blinded. Follow-up questionnaires will be primarily conducted online or sent via post. However, some participants may prefer to complete their questionnaire by telephone. Where possible, staff members involved in collecting outcome data during follow-up will be blinded to allocation.

## Data collection and management

### Plans for assessment and collection of outcomes {18a}

Plans for the collection of baseline and outcome data are detailed in Table 1. Data collection forms can be found in Additional files 1 (Baseline Questionnaire) and 7, 8, 9 and 10 (3 m, 6 m, 9 m and 12 m Outcome Questionnaires).

**Table 1 Tab1:**
[figure not shown]
Participant timeline

The following questionnaires will be completed at baseline, following registration but prior to randomisation, by participant self-completion online (or researcher administration if preferred by participant):Clinical Outcomes in Routine Evaluation—Outcome Measure (CORE-OM) is a 34-item measure, used to assess levels of psychological global distress across four dimensions of well-being, symptoms (depression, anxiety, physical and trauma), functioning and risk [36]. The CORE-OM is acceptable to participants to complete and is widely used in primary and secondary care services in the NHSHopelessness—Beck Hopelessness Scale is a 20-item self-report inventory and is used to measure feelings about the future, loss of motivation, and expectations [30, 37]Depression—PHQ-9 is a is a 9-item self-report measure of depression severity used to assess mental and emotional conditions, providing a reliable and valid measure of depression severity [38]Social connectedness—The Social Connectedness Scale-Revised is a 20-item scale used to measure social connectedness as a sense of belonging [29, 39]Self-reported resource use—primary and community care and medications and private financial burden due to self-harm (trial-specific).

Follow-up questionnaires will be completed at 6 and 12 months post-randomisation (to coincide with the anticipated end of therapy and at least 6 months after the end of therapy). The default method will be web-based completion, but paper copies can be posted out to participants if preferred. The following data will be collected at 6 and 12 months: Clinical Outcomes in Routine Evaluation—Outcome Measure (CORE-OM), Beck Hopelessness Scale, PHQ-9, the Social Connectedness Scale-Revised, self-reported episodes of self-harm, self-reported resource use—primary and community care and medications and private financial burden due to self-harm (trial-specific). In addition, participants will be asked to report on health resource use at 3 and 9 months, as recall over periods longer than 3 months may be suboptimal.

### Plans to promote participant retention and complete follow-up{18b}

To maximise participant retention and follow-up, the following measures will be implemented:Collection of data enabling multiple methods of data collation and contacting participants (email, post, phone);Those who do not complete the questionnaires will receive one automated reminder to prompt completion, followed by further reminders via telephone from a researcher who will also offer to support data collection over the telephone;A financial incentive will be offered for completion of 6-month questionnaires (£20 online voucher) and 12-month questionnaires (£40 voucher);A letter from the Lived Experience Group will also be sent to participants at 6- and 12-month time points with thanks and encouragement to continue engagement with the project;Researchers embedded within each healthcare organisation will deliver the trial and liaise with participants and therapists to facilitate retention.

### Data management {19}

Data will be recorded by researchers and site staff using a combination of trial-specific paper case report forms (CRFs) and remote data entry. Data recorded on paper CRFs, for example during face-to-face visits at baseline, or by therapists after therapy sessions, will be entered into a Remote Data Capture database by researchers or therapists at site or returned by post to Leeds CTRU, as per instructions supplied to sites.

Participant could opt to compete questionnaires online using REDCAP survey software, by post, or by telephone with a researcher. Participants who did not respond to the initial questionnaire were sent a reminder after 10 days. Participants who did not respond to the reminder questionnaire were contacted by telephone and were encouraged to complete the questionnaire with the option to complete it over the phone.

Relevant standard operating procedures, guidelines and work instructions in relation to data management, processing and analysis of data will be followed. At the end of the study, data will be securely archived at the University of Leeds for a minimum of 5 years. Data held by the University of Leeds will be archived in the Leeds Sponsor archive facility, and site data and documents will be archived at site. Following authorisation from the sponsor, arrangements for confidential destruction will then be made.

Data collected through observations (field notes and observational records, audio recorded interviews, summaries of documentary analysis) and reflective reports will be anonymised and stored at the Leeds Institute of Health Sciences, University of Leeds.

### Confidentiality {27}

All information collected during the course of the study will be kept strictly confidential. Information will be held securely on paper and electronically at the CTRU. The CTRU and LIHS will comply with all aspects of the 2018 Data Protection Act. Participant name, address and telephone number will be collected when a participant is registered into the trial, but all other data collection forms that are transferred will be coded with a trial number and will include two participant identifiers, usually the participant’s initials and date of birth. All records that contain personal identifiers, such as informed consent and contact details forms, will be stored separately from study records identified by Trial ID code.

Appropriate processes will be put in place for the transfer, storage, restricted access and disposal of personal information. To ensure confidentiality of the data collected when published, fictitious site names and pseudonyms or study numbers not linked to sites or persons will be used. All identifiable data such as research site names, address, date of birth and participants’ names will be removed.

### Plans for collection, laboratory evaluation and storage of biological specimens for genetic or molecular analysis in this trial/future use {33}

This is not applicable; no specimens were collected.

## Statistical methods

### Statistical methods for primary and secondary outcomes {20a}

A detailed statistical analysis plan will be finalised and agreed by the research team prior to analysis.

A single final analysis is planned after the trial is closed to recruitment and follow-up and when the full database has been cleaned and locked. Analyses will be completed by the CTRU statisticians using SAS version 9.4.

The primary analysis of CORE-OM will use mixed multilevel linear regression with repeated measures (6- and 12-month outcome) adjusted for randomisation stratification factors and baseline value, with therapist treated as a random intercept. Estimated mean treatment differences at each time point will be reported with 95% confidence interval, *p*-values and ICCs. A two-sided 5% significance level will be used for statistical endpoint comparisons, unless otherwise specified.

Secondary outcomes, reliable and clinically significant improvement on the CORE-OM, hopelessness, depression and social connectedness will be analysed using the same approach, i.e. mixed multilevel linear or logistic regression, depending on the type of outcome variable.

Secondary outcomes repetition of self-harm leading to hospital and self-reported repetition of self-harm will be analysed separately.

Cox proportional hazards, accounting for randomisation stratification factors and random therapist effect (multilevel survival frailty model) [40], will be used to test for differences in the time to first repetition and the proportion of participants attending hospital for self-harm at 6 and 12 months. Hazard ratios and corresponding 95% CIs will be presented. If a participant is lost to follow-up, they will be treated as censored. Kaplan–Meier curves will be constructed for each group.

Recurrent event analysis incorporating the timing and cumulative number of hospital attendances for self-harm will be used to test for differences in the rate of recurrent events. Estimated treatment differences will be reported as the hazard ratio with 95% confidence interval and *p*-values.

Self-reported self-harm will be summarised at each follow-up time point (monthly to 12 months).

The number of episodes of self-reported self-harm at 6 and 12 months from questionnaires (supplemented by monthly SMS data) will be analysed using Poisson regression, if appropriate. This will be a secondary method for the assessment of self-harm repetition. The choice of analysis method for self-reported self-harm will be informed by the data from the feasibility study.

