## Introduction

### Background and rationale {6a}

Self-harm is a major public health challenge with estimated lifetime prevalence of 5–6% [1] and the reason for 220,000 hospital attendances annually in England and Wales [2]. Repetition of self-harm is common with 70% of those attending hospital following an episode of self-harm reporting previous episodes and about 25% who will then attend for a subsequent act during 18-month follow-up [3]. Up to 20% of those who present to hospital report a history of over five acts [3]. For those seen in hospital after an episode which represents at least their third attendance, more than 50% will go on to a further repeat attendance [2]. It is assumed that 40,000–50,000 hospital attendances a year are accounted for by those who repeatedly self-harm [4]. Most is known about hospital attendance because of ease of data collection, but as many episodes again do not lead to hospital attendance [4, 5].

Repeated self-harm is associated with depression and misuse of alcohol, poor quality of life and problems with interpersonal and social function [6], and the risk of suicide is higher for those with a history of repeated episodes [7]. Self-harm bears a significant cost both to the individual and the healthcare system. Repetition of self-harm accrues substantial treatment costs with each hospitalisation; meanwhile, costs rise significantly in the 6 months following hospital attendance following the fifth and subsequent episodes, compared to the first [8].

A Cochrane review showed little evidence for the benefit of existing therapies for people who self-harm multiple times [9]. Therapies that have been studied are intensive, of long duration, require specialist therapists, and there is no published evidence of cost-effectiveness. The latest Cochrane review, NICE guidelines in the longer-term management of self-harm in adults (CG133) [10] and expert commentaries [11] all point to the need for new research to test the effectiveness of interventions in this population.

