### Eligibility criteria {10}

Participants who have attended the ED following an episode of self-harm and who have received a detailed psychosocial risk assessment from a mental health practitioner will be screened for the study.

Inclusion criteria:Aged 18 years or over;Registered with a GP in the catchment area of the mental health trust for the duration of the therapy;Presenting at ED as a consequence of self-harm, defined as intentional acts that directly harm a person’s own body. This includes methods like cutting, burning, scratching, banging or hitting parts of the body or interfering with wound healing, and it also includes self-poisoning, such as taking overdoses of drugs;Self-harm episode in the preceding three months that is at least their third episode in the preceding 12 months and their lifetime fourth or more episodes;Has mental capacity to provide fully informed written consent.

Exclusion criteria:Receiving, or having been referred to (and likely to receive this within the next 6 months), a specific psychological intervention that is similar to the trial intervention, or where a specific intervention is indicated for a related condition (e.g. anorexia nervosa) and would conflict with trial participation;Taken part in the FReSH START Feasibility study;Assessed by a mental health clinician as currently unsuitable for therapy (e.g. in crisis; actively suicidal, unable to tolerate therapy, i.e. past talking treatments have resulted in severe deterioration of mental state, has a diagnosis of schizophrenia, autism, or other form of severe mental illness that would be a contraindication for the talking treatments in this study);Lacking capacity to comply with study requirements;Insufficient proficiency in English to contribute to the data collection;Known risk of violence (for example reported by ED or liaison psychiatry staff);Researcher unable to contact potential participant within six weeks following self-harm event.

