### Outcomes {12}

The primary outcome measure is the difference between the two randomised groups in mean CORE-OM score at 12 months [28]. The CORE-OM is a 34-item measure, widely used in primary and secondary care services in the NHS to assess levels of psychological global distress across four dimensions of well-being, symptoms (depression, anxiety, physical and trauma), functioning and risk [28]. Quality of life (QoL) is the most important patient-centred outcome as it can capture positive life changes—although reduction in the episodes of self-harm would be expected, one does not necessarily mediate the other. Secondary outcome measures include the Social Connectedness Scale (SCS) [29], the Beck Hopelessness Scale [30] and the PHQ-9 [31]. The SCS has been included as we argue that a valued goal is interpersonal in nature; therefore, achieving this through means other than self-harm will lead to more positive social connections which we know is associated with quality of life [32]. The PHQ-9 provides a reliable and valid measure of depression severity, and the Beck Hopelessness Scale as hopelessness has been shown to be a risk factor in suicidal behaviour [33].Secondary outcomes measures assessed at 6 and 12 months post randomisation (unless otherwise indicated) include difference in mean score on the CORE-OM at 6-months;Difference in the proportion of participants with reliable and clinically significant improvement on the CORE-OM (defined as a change of five or more in the clinical score and a change in score from the clinical to non-clinical range);Difference in mean score on the Beck Hopelessness Scale (BHS) [30], a 20-item self-report inventory used to measure feelings about the future, loss of motivation, and expectations;Difference in mean score on the Patient Health Questionnaire- 9 (PHQ-9) [31], a 9-item self-report measure of depression severity used to assess mental and emotional conditions;Difference in mean score on the Social Connectedness Scale—revised (SCS-R) [29], a 20-item scale used to measure social connectedness as a sense of belonging;Difference in rates of self-reported self-harm repetition measured monthly using questionnaires and also using monthly SMS messages for the 6-month follow-up period;Difference in the time to repetition of self-harm leading to hospital attendance using routinely collected data from Hospital Episode Statistics (A&E, emergency care, admissions, and outpatient datasets).

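### The Cox model for hospital repetition of self-harm names no baseline measure of past attendance; pre-specifying one would be a cheap, modest gain in efficiency on a secondary outcome

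*Protocol article*

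**What the plan says.** All references are to the protocol article; the statistical analysis plan is not shown.

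- **Outcomes {12}** lists as a secondary outcome "Difference in the time to repetition of self-harm leading to hospital attendance using routinely collected data from Hospital Episode Statistics".
- **Statistical methods {20a}** adjusts the primary CORE-OM model for the stratification factors and the baseline value. The other questionnaire outcomes follow the same approach. For hospital repetition a different set is named: "Cox proportional hazards, accounting for randomisation stratification factors and random therapist effect".
- **Sequence generation {16a}** describes minimisation "balanced on stratification factors of site, gender and baseline CORE-OM score", the last of these cut at 25. None of the three measures self-harm history.
- For repeated events, {20a} plans "Recurrent event analysis incorporating the timing and cumulative number of hospital attendances for self-harm" but states no covariates.
- **Background {6a}** reports, for hospital attenders in general, "about 25% who will then attend for a subsequent act during 18-month follow-up". For people at a third or later attendance it says that "more than 50% will go on to a further repeat attendance", with no time window.
- **Eligibility {10}** requires a recent episode that is "at least their third episode in the preceding 12 months and their lifetime fourth or more episodes". This counts episodes, not attendances.

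**The concern.** Number of attendances is an outcome with an obvious baseline counterpart: attendances before randomisation. It is nevertheless modelled without one, whereas the questionnaire scores have theirs. Leaving a prognostic covariate out of a Cox model moves the estimated hazard ratio towards 1 relative to the covariate-conditional one, and usually costs power. Cutting baseline CORE-OM at 25 also discards information.

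Hospital repetition is the repetition outcome taken from routine records rather than self-report, and the target now in force is a minimum of 348 participants (Trial status), against 565 in the sample size section. Precision is therefore limited, and an inexpensive way of recovering some of it deserves attention. What is at stake is the chance of detecting a real reduction in repeat attendance, not the validity of the test.

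**Working it through.** **No figure to reproduce.** The article gives no number of events, hazard ratio or power for hospital repetition; its power statement concerns CORE-OM only. Every effect input below is therefore an assumption.

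**Step 1: what the background rates can show.** If the two rates in {6a} covered the same period, the crude hazard ratio would be ln(1 − 0.50) / ln(1 − 0.25) = (−0.693) / (−0.288) = 2.4. But one rate is over 18 months, the other has no window, and the contrast is between third-or-later attenders and all attenders. It supports prognostic value in general. It does not measure how far one eligible participant differs from another.

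**Step 2: a generic prognostic covariate.** Simulated Cox models, 1:1, 12-month control risk 50%, conditional treatment hazard ratio 0.70, two-sided 5%, no clustering, N = 348, 1,500 trials per row:

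| Predictor | Power without | Power with |
|---|---|---|
| Binary, HR 1.5 | 60% | 60% |
| Binary, HR 2.0 | 59% | 61% |
| Binary, HR 2.4 | 53% | 57% |
| Graded, HR 1.5 per SD | 54% | 59% |
| Graded, HR 2.0 per SD | 48% | 59% |

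In the last row the hazard ratio is 0.73 without and 0.70 with adjustment. Cross-check with the Schoenfeld formula: expected events = 348 × [0.50 + (1 − 0.5^0.7)] / 2 = 348 × 0.884 / 2 ≈ 154; power = Φ(√154 × |ln 0.70| / 2 − 1.96) = Φ(0.25) ≈ 60%. This matches the rows with a weak predictor. With no treatment effect (run at N = 565, binary HR 2.4) the mean hazard ratio is 1.00 and the rejection rate is 5.3% without and 5.7% with adjustment, so both tests are valid.

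**Step 3: prior attendances with eligibility applied.** Personal episode rates are gamma distributed (shape 0.5, 1 or 2), with mean yearly episode rates before selection of 1.5, 3 or 6. About half of episodes lead to attendance, in line with {6a}. Only people with at least 3 prior-year episodes and at least 1 attendance enter, following {10}. Rates are then recalibrated to a 50% control risk; N = 348 and the rate ratio is 0.65. Cox power (%) without / with the prior-attendance count, 800 trials per cell:

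| Shape | Mean 1.5 | Mean 3 | Mean 6 |
|---|---|---|---|
| 0.5 | 66 / 68 | 67 / 71 | 61 / 69 |
| 1 | 70 / 70 | 66 / 68 | 65 / 73 |
| 2 | 69 / 69 | 72 / 72 | 70 / 73 |

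The simulation error of one cell is about √(0.66 × 0.34 / 800) = 1.7 points. Gains in this grid run from 0 to 8 points. A separate run under the same selection rule gave about 0 to 13 points, under 6 in seven of nine scenarios, and no material loss anywhere. The hazard ratio moved by at most about 0.03. The wider range, 0 to 13, is the one to carry forward.

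**The case against.** The strongest reply is that this belongs in the statistical analysis plan. {20a} defers detail to that plan, extra prognostic covariates for a secondary outcome are commonly fixed there, and adjusting for the stratification factors is standard practice. That stands to this extent: the article contains no error or contradiction here, and the unseen plan may already add the covariate. The point survives as a suggestion because the article does name the covariates of the Cox model, so the plan would have to depart from the published list.

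The second reply is that the data are not documented. Hospital Episode Statistics are described for outcomes and admissions, no extract before randomisation is mentioned, and {10} sets a threshold without saying that a count is recorded. This also stands, and it makes the remedy conditional.

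Three stronger readings are tempting and are not supported:

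- *That the power loss is large.* A simulation without the eligibility floor gives Cox power of 39% against 63%, and 68% against 93% for the rate of attendances, at gamma shape 0.5. It sets the 12-month chance of no event at 50% and draws the prior-year count from the same personal rate, so half its participants have no attendance in the prior year. The trial recruits people who presented with self-harm and have at least three episodes in the year. Once that is imposed, the large Cox gain disappears. The rate figures rest on the same unselected population and cannot be relied on.
- *That the reported hazard ratio would be biased.* The gap is between a marginal and a conditional hazard ratio; under no effect both equal 1.
- *That the recurrent-event model also omits history.* Its covariates are simply not stated.

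**Conclusion.** The point holds as a modest improvement in efficiency. The Cox model as published has no baseline counterpart of its outcome, and adding one would probably help a little: roughly 0 to 13 points of power, mostly under 6, with a hazard ratio shift of at most about 0.03. These figures rest on assumed heterogeneity, a 12-month control risk of 50%, a rate ratio of 0.65, 348 participants, and half of episodes leading to attendance; therapist clustering and the stratification factors were left out. The upper end needs a strongly graded predictor, which the article cannot confirm within the trial. No figure is offered for the recurrent-event model. The primary analysis and the conduct of the trial are unaffected.

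**What to change.** In {20a}, or in the analysis plan before unblinded data are seen:

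1. Add log(1 + number of self-harm hospital attendances in the 12 months before randomisation) as a fixed covariate in the Cox model for hospital repetition.
2. State the covariates of the recurrent-event model and make them the same set.
3. In these models, enter baseline CORE-OM as a continuous score in place of the split at 25.
4. Take the count from a look-back in Hospital Episode Statistics if data access permits; otherwise use the episode count established at eligibility, if it was recorded, noting that it includes episodes that did not lead to hospital attendance.

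The cost is a sentence or two of plan wording, an earlier start date for the extract that may need data-access approval, and one extra degree of freedom. No participant contact is needed. Specifying it now matters because a covariate added after the data are seen would look data-driven.
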